## Abstract

**Background:**

Podcasts have emerged as a popular medium in medical education over the past decade. Audio learning allows flexibility and may help residents engage with content in new ways. Reading scientific literature is a core skill for residents, yet many residents struggle to comprehend complex research articles. Advances in artificial intelligence (AI) have enabled the automatic generation of podcast-style summaries of documents. It remains unclear whether listening to AI-generated podcast summaries can match the educational value of reading the full text of medical papers, and whether this depends on the complexity of the article.

**Objective:**

This study aims to compare comprehension of medical research papers when learning via an AI-generated audio podcast versus traditional reading. We will examine whether article complexity (narrative vs technical) moderates any difference. We hypothesize an interaction: for a highly complex article, residents who read the full text should achieve a better understanding than those who listen to a summary, whereas for an easier article, the difference between modalities should be smaller.

**Methods:**

We designed a 2×2 mixed factorial study with 60 resident physicians preparing for the board certification in internal medicine or cardiology. All participants will engage with 2 peer-reviewed cardiology articles differing in complexity: a narrative case report on eosinophilic myocarditis and a technical research article on quantifying the vena contracta area using 3-dimensional echocardiography. Each participant will read 1 article and listen to an AI-generated podcast summary of the other, with the order and assignment counterbalanced to control for order effects. The podcasts are created using Google NotebookLM’s experimental *audio overview* feature. Participants will complete a multiple-choice knowledge test for each article. The primary outcomes are comprehension scores for each modality. The secondary outcomes include intrinsic motivation, perceived learning gains, and cognitive load for each condition. Data will be analyzed using a mixed ANOVA to test the main effects of modality and article complexity, as well as their interaction.

**Results:**

Data collection is expected to be completed by early 2026. We will report the trial results according to the CONSORT (Consolidated Standards of Reporting Trials) guidelines, and any deviations from this protocol will be documented and justified. No results are available at the time of publication of this protocol.

**Conclusions:**

This randomized trial will offer evidence on the effectiveness of AI-generated podcast summaries as a learning tool for medical literature. If listening to an AI-generated podcast yields comprehension comparable to or superior to reading the full article, it could validate an innovative, time-saving approach for busy medical trainees. Conversely, if significant deficits are observed in the podcast group (especially for complex content), the findings will highlight the limitations of AI summaries and the continued importance of traditional reading for thorough understanding.

**International Registered Report Identifier (IRRID):**

PRR1-10.2196/78505

## Introduction

Medical education is increasingly embracing digital and asynchronous learning modalities. Podcasts, in particular, have seen a marked rise in their use as supplementary learning tools across many medical specialties. By 2021, an estimated 41% of Americans reported listening to a podcast in the past month [1], and medical education has mirrored this trend with numerous educational podcasts now available for both trainees and practitioners [2,3]. For medical residents, podcasts offer a convenient way to learn on the go and can introduce clinical topics in an engaging, conversational format [4]. The popularity of podcasts suggests that they may help sustain learners’ interest and motivation [5]. However, it is important to evaluate whether learning medical content via podcasts is as effective as more traditional methods.

One traditional learning activity in medical school is reading and appraising journal articles. The ability to read and comprehend scientific papers is fundamental for evidence-based practice and lifelong learning [6]. However, medical residents often find it challenging to digest primary literature, especially when articles are dense or highly technical [7]. Journal club studies have documented that learners struggle to understand complex research papers, sometimes becoming lost in advanced methodologies or jargon [7]. Practical, case-based articles (eg, clinical case reports or case-based discussions) may be easier to follow, as they tend to have concrete patient narratives and applied lessons [8]. In contrast, theoretical or review articles (eg, a detailed review of endocrine pathophysiology) can be abstract, laden with data, and not immediately relatable to clinical practice. This disparity in content complexity could influence how well learners comprehend the material and stay engaged [9].

Beyond accessibility and learner motivation, self-regulation theory [10] predicts that podcasts may offer educational advantages related to repetition, self-pacing, and multitasking [11] if learners are able to use them appropriately. However, using podcasts to access medical journal articles may yield higher cognitive demands than reading the articles. The interplay between cognitive resources and learning outcomes is central to cognitive load theory, which posits that human working memory has a limited capacity crucial for learning [12]. According to cognitive load theory, learning activities typically demand a significant allocation of cognitive resources, and instructional design plays a pivotal role in either exacerbating or alleviating cognitive load. The theory delineates 3 types of cognitive load: extraneous, intrinsic, and germane, each influencing learning in distinct ways [13]. Listening to audio differs cognitively from reading: listeners process information sequentially, at a fixed pace, and may lack easy access to figures or references [14]. In addition, podcasts are inherently reductive; condensing full-text articles into short conversational scripts may reduce extraneous load [15] but risks omitting critical nuance or context [16,17]. This, in turn, may suppress the intrinsic load necessary for deeper understanding, ultimately resulting in shallow learning processes [15]. While learners may perceive these summaries as more enjoyable or efficient, it is unclear whether they support equivalent knowledge acquisition, especially for content of varying complexity.

Producing high-quality medical education podcasts typically requires expert knowledge, pedagogical insight, technical skills, and significant time for scripting, recording, and postproduction [18]. These constraints limit scalability and personalization, especially for institutions or learners aiming to integrate podcasts into dynamic, content-rich environments, such as medical curricula. Recent advances in generative artificial intelligence (AI) present an opportunity to overcome some of these barriers. AI-powered systems based on large language models can now generate podcast-style summaries of academic content by transforming articles into structured, conversational dialogues [16]. These AI-generated podcasts often simulate discussions between 2 virtual hosts, aiming to translate complex material into an engaging audio narrative. Early research indicates that such podcasts can enhance learner motivation and satisfaction, particularly when personalized according to user needs [19]. Some studies suggest comparable or even superior learning outcomes relative to traditional reading in specific contexts [17,19].

Nevertheless, the educational value of these AI-generated summaries remains largely untested in medical education [18]. AI-generated podcasts may lack the necessary accuracy or lose important contexts, which may cause either worse learning outcomes or potentially even misinform learners and endanger patients. Therefore, this study aims to address these questions through a randomized controlled trial comparing learning outcomes across 2 types of medical articles (practical vs theoretical) in the reading and listening modalities. By examining both knowledge acquisition and learners’ motivational and cognitive responses, we aim to assess whether AI-generated podcasts can serve as a viable tool for engaging residents with scientific literature.

The primary objective of this randomized trial is to compare knowledge acquisition from medical journal articles between 2 learning modalities: listening to an AI-generated podcast versus reading the full text. We seek to determine if one modality leads to superior comprehension in medical residents. A secondary objective is to assess the influence of article complexity on learning outcomes and any interaction between complexity and modality.

In operational terms, the study will test two main hypotheses and one interaction hypothesis, as presented in Textbox 1.

Study hypothesis.**Main effect of modality (artificial intelligence [AI]**–**generated podcast vs reading the full text)**There may be a difference in knowledge scores between residents who listen to an AI-generated audio summary and those who read the article, regardless of complexity. We will explore the direction of this effect; we expect that reading the full article could confer an advantage for understanding, especially detailed content, but well-crafted audio summaries may yield comparable results for certain types of information.
**Main effect of complexity (low vs high)**
We anticipate that all residents, regardless of modality, will find the *complex* article more challenging, resulting in lower average test scores compared to the *easy* article, given the higher theoretical density of the former.
**Modality × complexity interaction**
We hypothesize an interaction such that the effectiveness of the podcast relative to reading will differ by article complexity. Specifically, the performance gap (if any) between listening and reading is expected to be larger for the complex article than for the easy article. In other words, for the easier, case-based article, listening to a summary might achieve nearly the same comprehension as reading, whereas for the complex article, listening to the summary might not capture enough detail, leading to lower comprehension compared to reading the full text.

Additional objectives include evaluating secondary outcomes related to the learning experience: we will compare residents’ intrinsic motivation during the task, subjective cognitive load, and their subjective perception of learning between the 2 modalities. This will provide a more nuanced understanding of how engaging or difficult residents found the learning process in each condition, beyond the factual knowledge gains. Ultimately, the goal is not only to determine which method yields higher test scores, but also to consider which method residents prefer or find more motivating, because an engaging learning experience could encourage more frequent interaction with the scientific literature.

## Methods

All study materials (articles, audio files, and questionnaires) and deidentified data will be made available in an open science repository [20] upon study completion, in line with open science practices.

### Study Design and Setting

We will conduct a single-center, 2-factor mixed experimental study with a 2×2 design. The within-subjects factor is the learning modality (AI-generated podcast vs traditional reading), and the between-subjects factor is the presentation order (ie, which article-modality combination comes first). Each participant will engage with 2 cardiology articles—1 practical case report and 1 technical research paper—experiencing 1 via reading and the other via an AI-generated podcast. The assignment of modality to article and the sequence of presentation will be fully counterbalanced across participants to control for order effects and content bias.

The study will take place at LMU Munich. Each participant will attend a single study session, during which they will read 1 article and listen to the other in podcast form. After each learning task, participants will complete a multiple-choice knowledge test and questionnaires assessing motivation, cognitive load, and perceived learning.

All study sessions will be conducted in a controlled classroom environment at LMU Munich. A researcher will be present throughout the study to supervise the session and ensure adherence to the protocol. The physical setting will be quiet, with individual desks and study materials provided on desktop computers or tablets. Participants in the podcast condition will be provided with noise-canceling headphones to standardize audio delivery.

### Participants and Recruitment

The study population will consist of resident physicians enrolled in specialty training programs at LMU Munich, specifically those preparing for the German board certification (Facharztprüfung) in internal medicine or cardiology. These physicians have completed medical school and are engaged in postgraduate training, making them an ideal population for studying learning strategies that support lifelong engagement with scientific literature.

#### Sample Size Calculation

We conducted an a priori power analysis using G*Power (version 3.1; Heinrich Heine University) [21] for a mixed ANOVA with 1 within-subjects factor (learning modality: podcast vs reading) and 1 between-subjects factor (article-modality order). To detect a moderate effect size (f=0.25) for the main effects or interactions, with α=0.05 and power (1−β=0.80), the required total sample size is approximately N=44. To account for potential dropouts or missing data, we plan to recruit a total sample of N=60 resident physicians.

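### The 80% power claimed at N≈44 for main effects or interactions does not hold for the hypothesised modality×complexity interaction, which is a between-person contrast with 42–63% power at 44 and 54–77% at 60

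*Protocol article*

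**What the plan says.** All references are to the protocol article.

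- **Sample Size Calculation.** The power model is described as "for a mixed ANOVA with 1 within-subjects factor (learning modality: podcast vs reading) and 1 between-subjects factor (article-modality order". The target is "To detect a moderate effect size (f=0.25) for the main effects or interactions", "with α=0.05 and power (1−β=0.80". The result is that "the required total sample size is approximately N=44"; to allow for losses, "we plan to recruit a total sample of N=60 resident physicians". No within-person correlation and no number of groups are given.
- **Abstract, Objective.** "We hypothesize an interaction: for a highly complex article, residents who read the full text should achieve a better understanding", with a smaller difference expected for the easier article.
- **Textbox 1, Modality × complexity interaction.** The gap between listening and reading "is expected to be larger for the complex article than for the easy article".
- **Study Design and Setting.** Each participant meets both articles, "experiencing 1 via reading and the other via an AI-generated podcast". Which article goes with which modality is counterbalanced across participants.
- **Primary Analysis.** Modality, complexity and their interaction are all tested on the knowledge score. The model is called mixed, yet both listed factors are labelled within-subjects and no between-subjects factor is listed.
- **Descriptive Statistics.** Only complete cases are used.

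**The concern.** The sample-size sentence makes one power claim for every effect in the model. In this design the effects do not share an error term. Modality and complexity are each estimated from the difference between a person's two scores, so a positive correlation between those scores helps. The modality×complexity interaction is estimated from the sum of a person's two scores, compared between pairing groups, so the same correlation hurts. A sample size that suits the first kind of effect cannot be assumed to suit the second.

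At stake is how a null result is understood. The interaction is the hypothesis stated in the abstract and is tested in the primary analysis. A reader who accepts 80% power will give a non-significant interaction more weight than it can bear. The Discussion (Anticipated Findings) considers supporting wider use of AI audio if comprehension proves equivalent even for technical articles, so this is where an inflated power figure could mislead.

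**Working it through.** **Inputs from the document:** f=0.25, α=0.05, power 0.80, N=44 and N=60, two scores per participant.

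**Assumptions:** equal pairing groups, equal variances, and ρ between a participant's two scores. As ρ is not stated, the range 0 to 0.7 is shown.

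**Step 1: which contrast is the interaction?** Let R and P be read and podcast, and n and t the narrative and technical articles. Group A reads n and hears t; group B hears n and reads t.

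(Rn − Pn) − (Rt − Pt) = (Rn + Pt) − (Pn + Rt)

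The right-hand side is group A's summed score minus group B's summed score, a purely between-person comparison.

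**Step 2: formulas** (noncentral F, df 1 and N−2).
- Within-person effect: λ = 2f²N/(1−ρ).
- Between-person effect: λ = 2f²N/(1+ρ). Check: a person's mean score has variance (1+ρ)/2 in SD² units and the groups differ by 2f, so λ = (2f)² ÷ [(4/N)(1+ρ)/2] = 2f²N/(1+ρ).

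At N=44, 2f²N = 2×0.0625×44 = 5.5. At N=60 it is 7.5.

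**Step 3: the plan's own figure.** For a within-person test with two groups, N for 80% power is 66 (ρ=0), 46 (0.3), 44 (0.35) and 34 (0.5). So N=44 is reproduced at ρ≈0.35, where λ = 5.5/0.65 = 8.46 and power is 81.1%. At ρ=0.3 power at 44 is 78.2%; the 80% line is crossed at ρ of about 0.33. A four-group, 3-df modality×group test also gives 44, at ρ of about 0.56 to 0.58. That too is a within-person test.

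**Step 4: the modality×complexity interaction at f=0.25.**

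| ρ | λ at 44 | Power at 44 | λ at 60 | Power at 60 | N for 80% |
|---|---|---|---|---|---|
| 0 | 5.50 | 63.0% | 7.50 | 76.8% | 66 |
| 0.3 | 4.23 | 52.0% | 5.77 | 65.6% | 84 |
| 0.35 | 4.07 | 50.5% | 5.56 | 64.0% | 88 |
| 0.5 | 3.67 | 46.5% | 5.00 | 59.4% | 98 |
| 0.7 | 3.24 | 42.0% | 4.41 | 54.2% | 110 |

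A simulation of 20,000 runs at ρ=0.5 gave 46.3% and 59.4%. Modelling sequence as well (four groups, a 1-df contrast, N−4 df) gave 46.4% and 59.4%.

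**Step 5: detectable size.** At ρ=0.5 the smallest f with 80% power is 0.374 at N=44 and 0.319 at N=60. An interaction of size f puts the four cells at ±f SD. The reading–podcast gap is then 2f in one direction for one article and 2f in the other direction for the other, so the gaps differ by 4f. That is 4×0.374 = 1.50 SD at N=44 and 4×0.319 ≈ 1.27 SD at N=60. The planned f=0.25 is itself a gap difference of 1.0 SD.

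**Step 6: losses.** Falling from 60 to 44 is a loss of 16/60 = 26.7%. Because only complete cases are analysed, the N=60 column is the best case.

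**The case against.** **The interaction meant may be modality×order group.** The power model has modality within and article-modality order between, so its own interaction is a within-person test for which N≈44 is obtainable. This is a fair account of how the figure may have arisen, and it makes the defect a mismatch of model and hypothesis rather than a slip of arithmetic. It does not rescue the claim. If the groups are defined by pairing, the modality×group term is (Pt − Rn) − (Pn − Rt) = (Pt + Rt) − (Pn + Rn), which is the complexity main effect. If they are defined by sequence alone, it is a period effect. Neither is the interaction in the Objective and Textbox 1.

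**The interaction is not the primary objective.** The Introduction makes modality the primary objective and places complexity and its interaction under a secondary one. This stands. A reader might infer that the trial is underpowered for its main question, and the document does not support that: the modality effect has 81.1% power at N=44 if ρ=0.35 and 90.0% if ρ=0.5.

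**The unstated ρ may sit in the full protocol.** This is also fair, so its absence from a condensed article is not the finding. The conclusion does not depend on its value.

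**No misreading is planned.** A reader might infer that the investigators will treat a non-significant interaction as equivalence. The document does not say so, and Secondary Analyses commits to weighing effect size as well as the P value in all analyses. The misreading is a risk, not a stated intention.

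**Conclusion.** The point holds in this form: the 80% power statement is wrong for the hypothesised modality×complexity interaction. At f=0.25 its power is 42–63% at N=44 and 54–77% at N=60 for ρ between 0.7 and 0, and 80% would need 66 to 110 participants. No ρ≥0 brings it to 80% at either sample size. The shortfall at 60 is small if ρ is near 0 and large if ρ is 0.5 or more, so no single pair of figures should be quoted without its ρ. For example, 47% and 59% belong to ρ=0.5, not to the ρ≈0.35 that reproduces N=44 in a two-group within-person test.

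The result rests on equal pairing groups, equal variances and f scaled to the SD of a single score. Calling f=0.25 moderate is a conventional label and not an error, although its meaning here, a 1.0 SD difference between gaps, is worth stating.

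**What to change.** 1. **Sample Size Calculation.** State the assumed ρ. Limit the 80% claim to the within-person effects, and note that at N=44 these need ρ of at least about 0.33 to 0.35.
2. **Same section.** Give the modality×complexity interaction's power or detectable size at N=44 and N=60 as a range over ρ, using the Step 4 table or, for example, f≈0.32 (a gap difference of about 1.27 SD) at N=60 and ρ=0.5.
3. **Primary Analysis.** Correct the labelling. Each participant meets both levels of each factor but not all four cells, so the model needs the pairing group as a between-subjects factor, and the interaction must be tested against between-person error.
4. **Reporting.** Give the interaction with a 95% CI, and state that a non-significant result will not be read as absence of moderation.

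The cost is a few sentences and a less favourable power statement. No extra participants are required. The Results section says that none had been recruited at submission, so the correction can be made before any data exist if that is still the case.

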#### Inclusion Criteria

Participants must be currently enrolled in a medical residency program, specifically in a discipline such as internal medicine or cardiology. Additionally, they must be actively participating in a structured preparation course for the German specialist board certification (Facharztprüfung). Eligible participants should have completed their undergraduate medical education and be in the clinical phase of a postgraduate training.

Because the study materials, including the articles and AI-generated podcast summaries, are presented in English, participants must have sufficient English proficiency to understand both written and spoken academic medical content. While we expect most physicians in the preparation course to possess the necessary language skills, this will be confirmed informally during recruitment.

All participants must be willing and available to participate in a single research session lasting approximately 60 minutes and must provide written informed consent. Furthermore, they must have normal or corrected-to-normal hearing and vision to ensure that they can engage with both the reading and audio conditions, as required by the within-subjects design.

#### Exclusion Criteria

We will exclude individuals who have prior extensive familiarity with the specific articles used in the study. During recruitment and again at the start of the experimental session, we will present the titles and journal references of the 2 articles. If a participant confirms that they have previously read, studied, or discussed either article in detail (eg, in a journal club or as part of examination preparation), they will be thanked and excluded from participation to avoid a knowledge bias.

Additionally, individuals with uncorrected hearing impairment or severe visual impairment that would prevent them from effectively listening to the audio podcast or reading the article will be excluded. Because each participant will engage in both a reading and a listening task, we require all participants to have unimpaired or corrected functional access to both modalities.

We will recruit participants from a structured board examination preparation course organized by LMU Munich. This course attracts physicians actively preparing for their specialty certification and therefore reflects a highly motivated and relevant target group. Participants will be informed about the study through announcements made during the course sessions and follow-up emails. The study will be presented as a research project on learning from medical articles using different formats, without disclosing specific hypotheses. Participation is entirely voluntary and will not affect their standing in the course or the certification process.

Before participation, each physician will receive a full briefing on the study’s goals, procedures, and data privacy protections. This study will generally be described as a comparison of different learning formats for medical content. Written informed consent will be obtained. We will emphasize that participation is voluntary, performance on the comprehension tests has no bearing on their training or certification, and all data will be anonymized and treated confidentially.

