### Study Materials

#### Articles (Learning Content)

Two published medical articles have been selected to represent different levels of complexity within the field of cardiology, both published in *BMC Cardiovascular Disorders*.

The *narrative* article is a case-based clinical report [22]. This report describes the diagnostic journey and clinical management of a patient with eosinophilic myocarditis who presented with cardiogenic shock and malignant arrhythmias. The article is structured in a narrative format and emphasizes clinical reasoning, interdisciplinary care, and escalation of treatment. It presents practical, concrete decision-making steps, making it highly accessible and relevant for clinical-phase medical students.

The *technical* article focuses on the validation of 3-dimensional echocardiographic measurements of the vena contracta area for quantifying mitral regurgitation severity [23]. It involves advanced imaging techniques, direct planimetry, multiplanar reconstruction, and statistical comparisons, including sensitivity and specificity analysis and Bland-Altman plots. The dense methodological content and reliance on imaging expertise and statistical interpretation make it cognitively demanding and better suited for advanced learners with prior knowledge of cardiac imaging and valvular pathology.

These articles were deliberately chosen to provide a clear contrast in complexity and content delivery within the same specialty and text length (8 pages), allowing for an effective assessment of learning outcomes across different formats and difficulty levels.

For the reading groups, the article text will be provided on a screen in PDF format. For the podcast groups, the content of these articles is used as input to generate the AI podcasts.

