#### Orientation (5 Min)

Participants are welcomed and seated at a computer or tablet station. Written informed consent is obtained if not already collected during recruitment. Participants then complete a short intake form to gather demographic information (age, gender, and specialty area), confirm their participation in the Facharztprüfung preparation course, and verify their English proficiency and lack of prior exposure to the study materials. They are also screened for any sensory impairments that might interfere with reading or listening tasks.

Participants are randomly assigned to one of the counterbalanced order conditions (ie, whether they first read the narrative article or listen to the technical podcast, or vice versa). The researcher then provides access to the appropriate learning material.

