#### Informed Consent

As noted, we obtain written informed consent from all participants. They are informed that the study is about learning from the medical literature and involves completing tests, but the full details of the interventions are somewhat masked until debriefing to preserve the blinding of the hypothesis. They are told that they can withdraw at any time without penalty.

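### Naming both articles at recruitment gives candidates an avoidable opportunity to read them before the session, and the later self-report check may miss it

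*Protocol article*

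**What the plan says.** Under Exclusion Criteria, the protocol article describes two screens for prior familiarity: "During recruitment and again at the start of the experimental session, we will present the titles and journal references of the 2 articles". The exclusion is triggered by the participant's own report: "If a participant confirms that they have previously read, studied, or discussed either article in detail". The consequence and its purpose follow: "they will be thanked and excluded from participation to avoid a knowledge bias".

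The Orientation section adds an intake form at session start, completed before random assignment, which must "verify their English proficiency and lack of prior exposure to the study materials".

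Four other statements bear on the point:

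- The materials are in print: "Two published medical articles have been selected to represent different levels of complexity within the field of cardiology".
- Recruitment is separate from the session: "Participants will be informed about the study through announcements made during the course sessions and follow-up emails". The interval between the two is not stated.
- Candidates know there will be a test: "They are informed that the study is about learning from the medical literature and involves completing tests".
- The source population is characterised thus: "This course attracts physicians actively preparing for their specialty certification and therefore reflects a highly motivated and relevant target group".

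The same Exclusion Criteria section also says that test results do not affect anyone's training or certification.

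**The concern.** The exclusion is meant to keep out people who already know the two papers. Giving the citations to candidates ahead of the session supplies what they need to acquire that knowledge. Nothing in the document asks them not to look the papers up in the meantime.

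What is at stake is the size of the main comparison. The podcast is a condensed account without figures or tables, as the Limitations section acknowledges. Someone who has already read both papers has the missing detail for the one they later hear, while for the one they later read they gain only a repeat. The reading-podcast difference would then tend to narrow. The hypotheses expect the larger gap for the technical article, so a loss there would also weaken the interaction. Under Anticipated Findings, equivalent comprehension would be taken as support for bringing AI audio into learning routines, so the likely error lies in the direction of a conclusion the authors would act on.

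**Working it through.** The plan gives no figure for pre-reading, so the check is mainly one of setting the sections against each other. The arithmetic is an illustration under stated assumptions.

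**1. Is disclosure at recruitment needed for the screening?** The same question is put again at session start (Exclusion Criteria), and the intake form precedes random assignment (Orientation). The later check therefore does the screening that matters. The earlier one saves booking someone who is already familiar with a paper.

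**2. What can the later check miss?** Exclusion Criteria removes those who report detailed prior engagement with a paper. Orientation asks for absence of prior exposure. A candidate who skimmed a paper after recruitment and says so passes under the Exclusion Criteria rule and fails under the Orientation rule. A candidate who does not say so passes under both.

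**3. Would undeclared reading show in the data?** The outcome is a post-task score of 0 to 10 per article, and the session procedure lists no pretest. It would not be visible.

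**4. Does the within-subjects design remove it?** Each participant meets a different article in each modality, so knowledge specific to one article does not cancel within a person.

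**5. Is it related to allocation?** Assignment follows screening at the session, so candidates cannot choose which paper to pre-read according to the modality in which they will receive it. Pre-reading is independent of allocation.

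**6. Size if pre-readers declare themselves.** Of 60 recruited, a share q is excluded and 60 × (1 − q) remain: 57 at 5%, 54 at 10%, 48 at 20%. The stated requirement of 44 is reached at q = 1 − 44/60 = 26.7%.

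**7. Size if they do not.** Assume a share q of analysed participants pre-read both papers and show no modality gap. The average difference becomes (1 − q) times its true value. A difference of 0.5 SD (illustrative) becomes 0.475 SD at 5% and 0.40 SD at 20%.

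For power, start from the planned f = 0.25, α = 0.05. With two order groups and two measurements, the within-subject test has 1 and N − 2 degrees of freedom and noncentrality λ = f² × N × 2 / (1 − ρ). The document does not state ρ, the correlation between the two measurements. The planned N of 44 at 80% power is reproduced with ρ of about 0.35: λ = 0.0625 × 44 × 2 / 0.65 = 8.46, power 0.81. Replacing f by 0.25 × (1 − q) gives:

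| q | f | Power, N=44, ρ=0.35 | Power, N=60, ρ=0.35 | Power, N=60, ρ=0.5 |
|---|---|---|---|---|
| 0 | 0.25 | 0.81 | 0.92 | 0.97 |
| 5% | 0.2375 | 0.77 | 0.89 | 0.95 |
| 10% | 0.225 | 0.73 | 0.85 | 0.93 |
| 20% | 0.20 | 0.62 | 0.76 | 0.86 |

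Both q and ρ are assumptions.

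**The case against.** The strongest reply is that the protocol already screens twice, and that the second screen would exclude a candidate who read a paper after recruitment and says so. The Orientation wording is wide enough to reach a skim. This stands, and it leaves two gaps: undeclared reading, and the mismatch between the two thresholds.

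The motive is also weak. The description of candidates as motivated refers to their own certification, not to this study's quiz. Scores carry no consequence, the only incentive is an optional voucher lottery with no stated link to performance, and nothing suggests that these two papers are examination content. This stands too, and it argues for a low expected frequency.

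Early screening has a practical use, since it spares familiar people a wasted session. That is true, but the benefit is small compared with the exposure it creates.

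A reader might infer that pre-reading is unbalanced across modalities. The documents do not support this, because allocation follows screening. What can differ is the effect of pre-reading, which probably helps more with the article heard as a summary. The shrinkage formula is also a ceiling, as long as pre-readers do not do better on the podcast article. They meet the other article a second time and may gain there as well, so some gap could persist.

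**Conclusion.** The point holds as an avoidable risk. Disclosure at recruitment opens a route to the knowledge bias that the exclusion is meant to prevent, the later check may not close it fully, and the data could not reveal a failure. The likely direction is a smaller reading-podcast difference.

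A reader might go further and infer that the procedure itself produces the bias. The documents show an opportunity only: they give no rate of pre-reading, no interval between recruitment and session, and little incentive.

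The size is therefore unknown. Under the assumed range of 5% to 20% undeclared pre-readers with no modality gap at all, the difference shrinks by at most 5% to 20%. At N = 60 and ρ = 0.35, power stays above 0.80 at 5% and 10% and falls to 0.76 only at 20%; at ρ = 0.5 it stays above 0.80 throughout. Declared pre-readers cost sample size only, and up to 20% of them would leave 48, above the stated 44. This is a cheap improvement to make before recruitment starts. It does not threaten the validity of the trial as designed.

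**What to change.** Three wording changes:

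- At recruitment, describe the materials only as two cardiology articles, without titles or references.
- Show titles and references once, at session start, before random assignment.
- Align Exclusion Criteria and Orientation on a single threshold: any prior reading of either article leads to exclusion.

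The cost is that a few people who already know a paper are identified only on the day and turned away. The margin between the required 44 and the planned 60, 16 participants, can absorb this, although it is also meant to cover dropouts and missing data. At submission no one had been recruited. The change has to be made before candidates are told the titles, because it cannot be undone afterwards.
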